## **13 BIOMARKER ANALYSES**

### **13.1 Plasma/PBMC**

Plasma and PBMC samples will be collected from the whole blood of each study subject at the time of biopsy collection; pre-dose and post-dose on Day 1, Day 15 and Day 29; and during study visits on Day 32, Day 43 and Day 57 (End of study). Plasma will be evaluated for cytokines and chemokines either by multiplex immunoassay (Luminex) or by single molecule counting (Singulex). PBMCs will be evaluated for the frequency of T cell subsets by flow cytometry. Whole blood gene expression analysis will be performed on samples collected using TempusTM tubes.

### **13.2 Skin Biopsies**

Skin biopsies will be taken from each study subject at: pre-dose (one each from psoriatic lesions and adjacent healthy skin for baseline) and on Day 32 (psoriasis lesions only). At each time, a biopsy of 6 mm will be taken and divided into two 3 mm pieces. If a single lesion of sufficient size is not available, two 4 mm biopsies may be collected from two similar lesions. Biopsies will be analyzed by histology (H&E) and immunohistochemistry for activation/cell-specific markers and by real time quantitative PCR to measure gene expression. Further details of sample collection and storage will be provided in a separate study manual.

## 14 STUDY PROCEDURES

### 14.1 Evaluations

Evaluations are summarized in [Appendix A](#). A central laboratory will perform all laboratory evaluations with the following exceptions:

- PK plasma sample analysis will be performed by Chimera Biotech;
- ADA evaluations will be performed by Kineta, Inc.;
- Plasma sample analysis for biomarkers by Luminex and Singulex will be performed by Myriad Genetics Inc. and the [name] laboratory (Rockefeller University), respectively;
- Skin biopsy samples will be processed and analyzed for histology, immunohistochemistry and gene expression by the [name] laboratory (Rockefeller University);
- Immunophenotypic evaluation of T cell subsets in PBMC samples will be performed by Kineta, Inc.;
- TEMPUS tubes with whole blood will be processed for RNA and evaluated by QPCR by Kineta Inc.

Every attempt will be made to perform evaluations on the scheduled day and time, as appropriate. Evaluations scheduled to occur on dosing days should be performed within the following post-dose intervals:  $5\pm 1$  min,  $15\pm 5$  min,  $30\pm 5$  min,  $1h\pm 10$  min,  $2h\pm 15$  min and  $4h\pm 15$  min. All of the post-dose procedures should be timed according to the time of dose administration. Evaluations scheduled to occur on non-dosing days through Day 29 should be performed on the day of the scheduled visit. Visits scheduled for beyond Day 29 should be performed within 1 day of the scheduled visit. Deviations from these times should be recorded in the CRF. Missed doses or significant alterations to the timing of a dose are permitted with the prior approval of the Sponsor.

A PPD or QuantiFERON-TB Gold test and chest X-ray will be performed at screening if it was not done within 6 months of Baseline (Day 1). PPD will be performed using 5 tuberculin units (5 TU). Reading will be performed 48 to 72 hours after PPD injection. An induration of 5 mm or more will be considered as positive. If the QuantiFERON-TB Gold test is chosen, it will be performed according to the manufacturer's instructions. Subjects who demonstrate evidence of latent TB infection (either PPD more than or equal to 5 mm of induration or positive Quantiferon Gold, irrespective of BCG vaccination status and negative CXR findings for active TB, and/or suspicious CXR findings) will not be allowed to participate in the study.

Neurological exams will be performed at screening, baseline and at the end of the study. Additional symptom-directed exams may be performed during the dosing period and at the completion of the follow-up period at the Investigator's discretion.

Additional evaluations, such as nerve conduction studies, may be performed in any subject for whom symptoms of paresthesia/peripheral neuropathy or new abnormalities in neurologic examination do not resolve off therapy.

#### 14.1.1 Screening Procedures (Day -30 to -1)

The following Screening procedures will be performed for all potential subjects at a visit

conducted within 30 days of baseline (Day 1, first dose):

1. informed consent;
2. medical and medication history (including pre-existing paresthesia and neuropathies);
3. demographic data;
4. weight, height, and BMI;
5. routine physical exam (including neurologic exam);
6. vital signs (including temperature, respiratory rate, and supine blood pressure and pulse);
7. 12-lead ECG;
8. assessment of psoriasis enrollment criteria: % BSA involved, adequate number of plaques of appropriate size and severity
9. clinical laboratory evaluations (including Chem-20 [fasted at least 4 hours], CBC, and UA; [Appendix H](#)); laboratory evaluations may be repeated if abnormal;
10. screens for HIV antibody, screen for hepatitis (HBsAb, anti-HCV), and screen for selected drugs of abuse ([Appendix H](#));
11. TB testing if not performed within 6 months of baseline (PPD or QuantiFERON-TB Gold and CXR);
12. serum pregnancy test (females only; [Appendix H](#)).

#### **14.1.2 Biopsy Procedures (Pre-dose, Day -7 to -1)**

Within one week of the first dose of study drug, subjects will present to the clinic to obtain a 6 mm punch biopsy of a psoriatic plaque (not the target lesion for assessment), as well as one 6 mm punch biopsy of healthy adjacent skin (at least 2.5 cm away from the lesion). Alternatively, two 4 mm biopsies may be collected if a single 6 mm biopsy cannot be obtained or if subject tolerability would be improved, as judged by the Investigator. Subjects will be instructed to abstain from the use of emollients for 24 hours prior to the scheduled biopsy/photography. Subject eligibility will be reviewed and randomization will occur prior to collection of biopsy tissue.

A target lesion for continued on-study assessment will be identified. Photographic documentation of the target lesion, biopsied lesion(s), location of healthy adjacent skin biopsy and psoriasis-involved body areas will be collected according to procedures described in the study manual.

Whole blood will be collected for biomarker analysis.

Subjects will be randomized.

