## **6.2 Subject Exclusion Criteria**

The following will exclude potential subjects from the study:

1. erythrodermic, predominantly guttate, exclusively palmar/plantar or generalized pustular psoriasis;
2. current drug-induced or aggravated psoriasis (*e.g.* a new onset of psoriasis or an exacerbation of psoriasis from beta-blockers, calcium channel blockers, or lithium carbonate);
3. use of the following concurrent systemic medications: corticosteroids, retinoids, cyclosporine, methotrexate or biologic agents. The wash out period for all these medications is 4 weeks or 5 half-lives prior to baseline, whichever is longer.
4. use of concurrent topical medications (must be discontinued at least 2 weeks prior to baseline);
5. UVA or UVB therapy within 4 weeks of baseline;
6. the presence of uncontrolled hypertension, uncontrolled diabetes, clinically significant (uncontrolled) cardiovascular disease, uncontrolled asthma or reduced pulmonary capacity or a history of seizure or other neurologic disorder;
7. presence or history of paresthesia or neuropathy;
8. abnormalities on neurologic exam at screening or baseline;
9. clinically significant ECG abnormalities in the opinion of the Investigator;
10. history of any cancer requiring systemic chemotherapy or radiation; individuals with a history of non-melanoma skin cancer, nonrecurring carcinoma in situ treated with laser or cryotherapy or cervical cancer-in-situ, resected surgically with no evidence of disease, may be accepted on a case by case basis at the discretion of the Investigator;
11. the presence of acute infection or history of acute infection as judged by the Investigator within 7 days of baseline; additionally, oral temperature may not exceed 37.4° C at baseline;
12. the presence of clinically significant laboratory abnormalities (chemistry panel of 20 analytes [Chem-20; fasted at least 4 hours], complete blood count [CBC], and urinalysis [UA]) as determined by the Investigator;
13. a positive hepatitis screen (Hepatitis BsAg or anti-HCV) or positive Human Immunodeficiency Virus (HIV) antibody test;
14. history of treated or untreated TB
15. any history of anaphylaxis that is important in the view of the Investigator;
16. participation in another clinical trial with receipt of an investigational product within 90 days of baseline (or 5 half-lives of the previous drug, whichever is longer);
17. history of alcohol abuse that is important in the view of the Investigator;

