#### **14.1.3 Baseline (Day 1, First-Dose) Procedures**

On Day 1, subjects will report to the study site and the following procedures will be performed.

Prior to Study Drug Administration (Predose Procedures):

1. interim medical and medication history;
2. routine physical examination (including neurologic exam);

3. weight;
4. vital signs (including temperature, respiratory rate, and supine blood pressure and pulse);
5. Review of subject eligibility
6. patient and Investigator global assessments of psoriasis§;
7. patient quality of life assessment (DLQI)§;
8. patient assessment of disability (using PDI)§;
9. %BSA involved and PASI§;
10. non-biopsied target lesion assessment§;
11. whole blood collection for biomarkers: PBMCs, plasma, serum and whole blood sample for RNA (TEMPUS TM);
12. clinical laboratory evaluations (including Chem-20 [fasted at least 4 hours], CBC, and UA);
13. baseline plasma sample for study drug concentration;
14. serum sample for assessment of antibodies to ShK-186;
15. urine pregnancy test (for females only); for female subjects to continue their participation in the study, the pregnancy test must be negative.

Study Drug Administration:

16. study drug will be administered and the start time of study drug administration will be recorded. Postdose study procedures will be based on study drug administration time.

Post-dose Procedures:

At 5 minutes post dose ( $\pm 1$  min):

17. plasma sample for study drug concentration.

At 15 minutes postdose ( $\pm 5$  min):

18. plasma sample for study drug concentration.

At 30 minutes postdose ( $\pm 5$  min):

19. vital signs (including temperature, respiratory rate, and supine blood pressure and pulse);
20. AE evaluations;
21. plasma sample for study drug concentration.

At 1 hour postdose ( $\pm 10$  min):

22. plasma sample for study drug concentration.

At 2 hours postdose ( $\pm 15$  min):

23. vital signs (including temperature, respiratory rate, and supine blood pressure and pulse);

---

§ Evaluation can be performed during the biopsy collection visit at Investigator's discretion.

24. AE evaluations;
25. plasma sample for study drug concentration;
26. whole blood collection for biomarkers: PBMCs, plasma, serum and whole blood sample for RNA (TEMPUS™).

At 4 hours postdose ( $\pm 15$  min):

27. plasma sample for study drug concentration.

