##### Prior to Study Drug Administration (Predose Procedures):

1. medication/medical history;
2. symptom directed physical examination;
3. vital signs (including temperature, respiratory rate, and supine blood pressure and pulse);
4. AE evaluations;
5. plasma sample for study drug concentration; [Day 15 only]
6. clinical laboratory evaluations (including Chem-20, CBC, and UA; [Appendix H](#));
7. serum sample for assessment of antibodies to ShK-186; [Day 15 only]

8. patient and Investigator global assessments of psoriasis; [Day 15 only]
9. patient quality of life assessment (DLQI); [Day 15 only]
10. patient assessment of disability (PDI); [Day 15 only]
11. %BSA, Psoriasis Area and Severity Index (PASI), and target lesion assessments; [Day 15 only]
12. whole blood collection for biomarkers: PBMCs, plasma, serum and whole blood sample for RNA (TEMPUS™). [Day 15 only]

Study Drug Administration (Time recorded)

Post-dose Procedures:

At 2 hours postdose ( $\pm 15$  min):

13. vital signs (including temperature, respiratory rate, and supine blood pressure and pulse);
14. AE evaluations;
15. whole blood collection for biomarkers: PBMCs, plasma, serum and whole blood sample for RNA (TEMPUS™). [Day 15 only]

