#### **14.1.8 Evaluations and Procedures on Day 32 and 43 Procedures**

The following procedures will be performed on Days 32 and 43:

1. interim medication/medical history;
2. symptom directed physical examination;
3. vital signs (including temperature, respiratory rate, and supine blood pressure and pulse);
4. AE evaluations;
5. patient and Investigator global assessments of psoriasis; [Day 32 only]
6. patient quality of life assessment (DLQI); [Day 32 only]
7. patient assessment of disability (PDI); [Day 32 only]
8. %BSA, Psoriasis Area and Severity Index (PASI), and target lesion assessments; [Day 32 only]
9. whole blood collection for biomarkers: PBMCs, plasma, serum and whole blood sample for RNA (TEMPUSTM);
10. skin biopsy (subjects will be instructed to abstain from the use of emollients for 24 hours prior to the scheduled biopsy/photography); [Day 32 only]
11. photographic documentation of target lesion that has been assessed throughout, biopsied lesion(s), as well as psoriasis-involved body areas. [Day 32 only]

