#### **14.1.9 End of Study Evaluations and Procedures (Day 57)**

The following procedures will be performed at the End of Study visit:

1. interim medication/medical history;
2. routine physical examination (including neurologic exam);
3. vital signs (including temperature, respiratory rate, and supine blood pressure and pulse);
4. AE evaluations;
5. patient and Investigator global assessments of psoriasis;

6. patient quality of life assessment (DLQI);
7. patient assessment of disability (PDI);
8. %BSA, Psoriasis Area and Severity Index (PASI) and target lesion assessments;
9. plasma sample for study drug concentration;
10. clinical laboratory evaluations (including Chem-20, CBC, and UA);
11. whole blood collection for biomarkers: PBMCs, plasma, serum and whole blood sample for RNA (TEMPUS™);
12. photographic documentation of target lesion that has been assessed throughout, biopsied lesion(s), as well as psoriasis-involved body areas (Subjects will be instructed to abstain from the use of emollients for 24 hours prior to the scheduled photography);
13. serum sample for assessment of antibodies to ShK-186;
14. serum pregnancy test (female subjects only);

Subjects that prematurely discontinue from study should complete all assessments for the scheduled visit and all End of Study assessments.

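### Psoriasis scores on Days 1 and 15 lack the 24-hour emollient rule that covers the biopsy visit, Day 32 and Day 57, and washouts run to Day 1 although baseline tissue is taken earlier

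*Protocol*

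**What the plan says.** **Emollient rule.** It appears in three visit lists, each time linked to biopsy or photography:
- Protocol 14.1.2 (Day -7 to -1): "Subjects will be instructed to abstain from the use of emollients for 24 hours prior to the scheduled biopsy/photography".
- Protocol 14.1.8 (Day 32): "skin biopsy (subjects will be instructed to abstain from the use of emollients for 24 hours prior to the scheduled biopsy/photography".
- Protocol 14.1.9 (Day 57): "Subjects will be instructed to abstain from the use of emollients for 24 hours prior to the scheduled photography".

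**Scoring visits.** Sections 10.1 to 10.7 and Appendix A place the disease scores on Days 1, 15, 32 and 57. The Day 1 list (14.1.3) has the global assessments, DLQI, PDI, %BSA, PASI and the "non-biopsied target lesion assessment". The Day 15 list (14.1.6) has "BSA, Psoriasis Area and Severity Index (PASI), and target lesion assessments; [Day 15 only" and the same global and questionnaire items. Neither day has a biopsy or photographs, and neither list mentions emollient.

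**Floating baseline.** A footnote to the Day 1 scores in 14.1.3, repeated in the synopsis, reads "Evaluation can be performed during the biopsy collection visit at" the Investigator's discretion.

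**Washout.** Exclusion criterion 4 in 6.2 bars "use of concurrent topical medications (must be discontinued at least 2 weeks prior to baseline". The same section sets 4 weeks for UV therapy, and 4 weeks or 5 half-lives, whichever is longer, for the listed systemic drugs. Section 7.2 repeats the topical and systemic periods. Sections 5.1.2 and 14.1.1 equate baseline with Day 1, the first dose. Section 13.2 and Appendix A footnote 6, however, also call the tissue taken on Day -7 to -1 baseline.

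**Use of the data.** Section 9.3 plans a descriptive evaluation of improvement from baseline at each scored timepoint and compares lesional biopsies with pre-treatment samples.

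**The concern.** Scaling enters PASI (Appendix C), the IGA (Appendix E) and the target lesion scale (Appendix G) directly. The protocol itself treats recent emollient as something to control before skin is photographed or sampled. It then leaves two of the four scoring days, including the default baseline day, without that control.

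Change from baseline is the planned summary, so a difference in skin condition between the two visits goes straight into it. The footnote allows the difference to vary from subject to subject within an arm.

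The second issue concerns tissue and any scores moved to the biopsy visit. If washouts end on Day 1 but baseline is sampled up to 7 days earlier, the baseline sample may fall inside the washout period that the protocol requires. The Day 32 sample cannot.

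**Working it through.** The protocol gives no figure for this point, and 9.4 says the sample size was not power-based. There is nothing to reproduce. The check sets the visits side by side and adds calendar and PASI arithmetic.

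**1. Emollient rule by scoring visit**

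| Visit | Scores taken | 24-hour rule |
|---|---|---|
| Biopsy visit, Day -7 to -1 | optional baseline | yes |
| Day 1 | default baseline | no |
| Day 15 | yes | no |
| Day 32 | yes | yes |
| Day 57 | yes | yes |

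Two consequences follow:
- Baseline scored on Day 1: the change to Days 32 and 57 compares an uncontrolled visit with a controlled one. If emollient reduced visible scaling on Day 1, improvement is understated.
- Baseline scored at the biopsy visit: the emollient condition matches Days 32 and 57, but not Day 15.

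For biopsies the rule is the same pre-dose and on Day 32, so emollient plays no part in the tissue comparison.

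**2. Illustrative size on PASI**

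Appendix C gives PASI = 0.1(E+I+D)A + 0.2(E+I+D)A + 0.3(E+I+D)A + 0.4(E+I+D)A over head, upper extremities, trunk and lower extremities. Assume area score A = 1 in all four regions and a shift of g scaling grades in each:

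- Change in PASI = (0.1 + 0.2 + 0.3 + 0.4) × 1 × g = 1.0 × g.
- g = 0 gives 0; g = 1 gives 1.0 point.
- With all signs at 2, PASI = 1.0 × (2+2+2) = 6, so the range is 0 to 1/6 = 17%.
- With all signs at 3, PASI = 1.0 × (3+3+3) = 9, so the range is 0 to 1/9 = 11%.

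The protocol gives no emollient effect, so g is an assumption, and 0 is possible.

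**3. Washout calendar**

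There is no Day 0 (Figure 1 note), so Day -7 is 7 days before Day 1, Day -1 is 1 day before it, and Day 32 is 31 days after it. Minimum days off treatment for a compliant subject:

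| Visit | Topicals (14 days to Day 1) | UV, or systemics under the 4-week limb (28 days to Day 1) |
|---|---|---|
| Day -7 | 14 - 7 = 7 | 28 - 7 = 21 |
| Day -1 | 14 - 1 = 13 | 28 - 1 = 27 |
| Day 1 | 14 | 28 |
| Day 32 | 14 + 31 = 45 | 28 + 31 = 59 |

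Where the 5-half-lives limb is the longer one, the shortfall is still at most 7 days, but a smaller share of the period.

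**4. Placebo group**

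Allocation 5:5:2 of 24 gives 24 × 5/12 = 10, 24 × 5/12 = 10 and 24 × 2/12 = 4 subjects.

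**The case against.** The strongest reply is that these rules are identical in every arm of a randomized, double-blind study. A reader might infer that the treatment comparison is biased. The documents do not support that: emollient use and timing of the baseline visit are not tied to allocation, so between-arm contrasts are not systematically distorted. The primary objective is safety, tolerability and immunogenicity, while disease activity is secondary and descriptive. All of this stands. It limits the harm to within-arm change and to variability, with about 4 placebo subjects to show how much change arises without drug.

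Other stronger readings also fail:
- *Biopsies are taken under different emollient conditions.* They are not; both tissue visits carry the same rule.
- *Baseline tissue carries residual treatment.* The washouts are minimums, so a shortfall is possible, not certain, and it falls to 1 day at Day -1. Nothing in the protocol shows a residual effect at 7 or more days off topicals.
- *The PASI figure is an expected bias.* It is a chosen scenario, and only subjects who actually used emollient could contribute to it.
- *Days 15 and 32 cannot be compared at all.* Emollient is permitted on Day 15, not required, and 9.3 plans change from baseline at each timepoint, not Day 15 against Day 32.
- *The footnote must go.* Once one emollient rule covers all scoring, and the washout passages are reconciled with that visit, keeping the option is largely a matter of preference.

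It could also be said that the ban on topical medications already covers emollients. The 24-hour instruction makes sense only if emollients are otherwise allowed. A separate study manual, not available here, may add detail; the protocol cites it for biopsy, photography and lesion selection, but not for scoring conditions on Days 1 and 15.

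**Conclusion.** The point holds in a limited form. Followed exactly, the protocol scores psoriasis on Days 1 and 15 without the emollient control in force at the biopsy visit and on Days 32 and 57, and allows baseline to come from either condition. The planned change from baseline therefore mixes skin conditions. The result is added variability and, for subjects who used emollient before a Day 1 scoring, a possible understatement of improvement in scaling. The illustrative size is 0 to 1.0 PASI point, resting on an assumed shift of 0 to 1 scaling grade and area score 1 in every region.

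Separately, baseline tissue, and optionally baseline scores, may be taken up to 7 days before the washouts must be complete. This rests on reading baseline in 6.2 and 7.2 as Day 1, as 5.1.2 and 14.1.1 define it.

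Neither issue threatens the randomized contrasts or the primary objective. Both are conditions of visit conduct fixed in the protocol, which later analysis cannot restore. They merit a cheap improvement.

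**What to change.** 1. Apply the existing 24-hour emollient instruction to every visit with psoriasis scoring: add it to 14.1.3 (Day 1), 14.1.6 (Day 15), the matching synopsis lists and a footnote on the scoring rows of Appendix A.
2. Reconcile the washout passages (6.2, 7.2 and synopsis) with the Day -7 to -1 visit at which baseline biopsies, and optionally baseline scores, are taken, so that it is clear which date the periods run to. The length of the washouts is a clinical matter on which this point takes no position.

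The cost is wording, 24 hours without emollient before two more visits, and slightly tighter scheduling of the biopsy visit. Sample size, arms and assessments are unchanged.

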#### **14.1.3 Baseline (Day 1, First-Dose) Procedures**

On Day 1, subjects will report to the study site and the following procedures will be performed.

Prior to Study Drug Administration (Predose Procedures):

1. interim medical and medication history;
2. routine physical examination (including neurologic exam);

3. weight;
4. vital signs (including temperature, respiratory rate, and supine blood pressure and pulse);
5. Review of subject eligibility
6. patient and Investigator global assessments of psoriasis§;
7. patient quality of life assessment (DLQI)§;
8. patient assessment of disability (using PDI)§;
9. %BSA involved and PASI§;
10. non-biopsied target lesion assessment§;
11. whole blood collection for biomarkers: PBMCs, plasma, serum and whole blood sample for RNA (TEMPUS TM);
12. clinical laboratory evaluations (including Chem-20 [fasted at least 4 hours], CBC, and UA);
13. baseline plasma sample for study drug concentration;
14. serum sample for assessment of antibodies to ShK-186;
15. urine pregnancy test (for females only); for female subjects to continue their participation in the study, the pregnancy test must be negative.

Study Drug Administration:

16. study drug will be administered and the start time of study drug administration will be recorded. Postdose study procedures will be based on study drug administration time.

Post-dose Procedures:

At 5 minutes post dose ( $\pm 1$  min):

17. plasma sample for study drug concentration.

At 15 minutes postdose ( $\pm 5$  min):

18. plasma sample for study drug concentration.

At 30 minutes postdose ( $\pm 5$  min):

19. vital signs (including temperature, respiratory rate, and supine blood pressure and pulse);
20. AE evaluations;
21. plasma sample for study drug concentration.

At 1 hour postdose ( $\pm 10$  min):

22. plasma sample for study drug concentration.

At 2 hours postdose ( $\pm 15$  min):

23. vital signs (including temperature, respiratory rate, and supine blood pressure and pulse);

---

§ Evaluation can be performed during the biopsy collection visit at Investigator's discretion.

24. AE evaluations;
25. plasma sample for study drug concentration;
26. whole blood collection for biomarkers: PBMCs, plasma, serum and whole blood sample for RNA (TEMPUS™).

At 4 hours postdose ( $\pm 15$  min):

27. plasma sample for study drug concentration.

